## Abstract

**Background:**

Cognitive flexibility (CF) enables individuals to readily shift from one concept or mode of practice/thoughts to another in response to changes in the environment and feedback, making CF vital to optimise success in obtaining goals. However, how CF relates to other executive functions (e.g., working memory, response inhibition), mental abilities (e.g., creativity, literacy, numeracy, intelligence, structure learning), and social factors (e.g., multilingualism, tolerance of uncertainty, perceived social support, social decision-making) is less well understood. The current study aims to (1) establish the construct validity of CF in relation to other executive function skills and intelligence, and (2) elucidate specific relationships between CF, structure learning, creativity, career decision making and planning, and other life skills.

**Methods:**

This study will recruit up to 400 healthy Singaporean young adults (age 18–30) to complete a wide range of cognitive tasks and social questionnaires/tasks. The richness of the task/questionnaire battery and within-participant administration enables us to use computational modelling and structural equation modelling to examine connections between the latent constructs of interest.

**Significance and Impact:**

The current study is the first systematic investigation into the construct validity of CF and its interrelationship with other important cognitive skills such as learning and creativity, within an Asian context. The study will further explore the concept of CF as a non-unitary construct, a novel theoretical proposition in the field. The inclusion of a structure learning paradigm is intended to inform future development of a novel intervention paradigm to enhance CF. Finally, the results of the study will be useful for informing classroom pedagogy and the design of lifelong learning policies and curricula, as part of the wider remit of the Cambridge-NTU Centre for Lifelong Learning and Individualised Cognition (CLIC).

## Introduction

As technology and globalisation are changing the nature of labour markets and increasing the demand for high skills levels, the need for individuals to be capable of learning new skills during their careers becomes increasingly pressing [1, 2]. In the Singapore context, where this study will take place, Singapore’s SkillsFuture programme, promoted by the Ministries of Education, Manpower, and Trade & Industry, aptly recognises that societies need workers with the capacity for flexible behaviour. That is, the ability to adapt to change, problem-solve in new situations based on previous experience to achieve in jobs that are likely to emerge over the next few decades [3]. This individual capacity for cognitive flexibility is central to the modern digital age with its rapidly changing settings at home and work [4, 5]. High cognitive flexibility is associated with improved wellbeing which will promote a flourishing society and will lead to improved social and workplace outcomes [6, 7] as well as entrepreneurship and innovation [8].

As we recognise the need for flexible behaviour and transferable skills in our workforce, we need our education systems to equip citizens with the cognitive flexibility they need to develop these skills for the future [9, 10]. However, there currently need to be more evidence-based training programmes that can effectively support and promote cognitive flexibility across the life course.

### Cognitive flexibility

Cognitive Flexibility (CF) is a component of executive function (EF), along with working memory and inhibitory control [11]. Existing studies encourage the view that there is something quite specific about the flexibility construct, making it separable from the other main EF components. The evidence for dissociations of CF and other executive functions comes from psychometric studies, genetic and neuroscientific investigations, and clinical findings (for recent reviews, see [12, 13]).

From the psychometric perspective, there is a general, well-known problem in measuring components of EF, which is that of "task impurity". Most cognitive tasks involve non-executive functions and commonly involve different loadings on its three prime components. Virtually all tasks have a working memory load, and most involve a degree of response inhibition. Importantly, Friedman and Miyake found that working memory updating has good relationships with measures of IQ (relevant to the general factor, *g*), but CF did not correlate highly with IQ measures [14]. Their recent review concluded, "all the studies we reviewed found evidence that shifting was separable from updating or working memory in older children and adults" [11]. They found that when inconsistencies did arise, they tended to involve the inhibition factor. Regarding relationships of shifting with response inhibition, Blackwell et al. found that children who were better at card sorting were worse at response inhibition [15]. A similar dissociation has been found for adults raised in stressful environments [16]. Therefore, although EF has a certain unity, there is also diversity, especially concerning CF.

Given the issue of "task impurity", to effectively measure the psychological construct of cognitive flexibility (as separate from other executive functions), it is necessary to administer multiple CF tests that load on the component of interest and to adopt a latent variable approach to analysis. With this method, Friedman and Miyake showed clear evidence of the separability of CF from other EFs [14]. This study showed that tests of CF ("shifting"), inhibition, and working memory have relatively low correlations with one another (representing an overall EF construct) but correlate well within each component. However, what is unknown–and would be a novel scientific advance–is whether cognitive flexibility itself may be further fractionated into sub-components (such as relating to rule learning and exploration as distinct from executive switching) and the extent to which different CF tasks tap into these sub-skills. In the current project, we seek to address this gap in understanding the nature and measurability of the cognitive flexibility construct to generate robust operational measures of CF for our later training studies.

In contrast to working memory and inhibition control, which are highly heritable skills, cognitive flexibility (CF) may be influenced more by environmental factors and potentially beneficial from training more effectively [11, 17]. Previous CF training interventions have used tasks that activate other executive functions, making them less precise as training tools [17–19]. To develop a training approach more precisely targeted at CF, we adopt the Structure Learning (SL) task, which involves identifying patterns in the presentation of stimuli without explicit feedback [20–23], as a foundational training paradigm (for more details about the SL task, see Methods section and Appendix D in S1 File). The SL training approach emphasizes the emergence of flexibility through exploring and rule learning generated in dynamic environments. SL training might lead to higher-order and potentially generalizable "learning-to-learn" abilities rather than rote memorization of specific information. We hypothesize that SL performance is associated with CF measures; thus, we include SL in the task battery and carefully examine its relationship with CF and other cognitive constructs.

A growing literature demonstrates links between CF and key outcomes of interest, particularly academic performance. For example, Yeniad et al. found that associations between shifting ability and reading and maths performance were "substantial and significant" [24], and Mayes et al. found that performance on the Wisconsin Card Sort Test–a prototypical test of cognitive flexibility was one of the very few measures that predicted maths performance, after accounting for general intelligence [25]. Accumulating data from these and other studies have provided largely correlational evidence and, to a lesser extent, developmental and intervention-based evidence for links between cognitive flexibility and “real-world” outcomes. However, few studies have adequately controlled for the effects of IQ and working memory (or inhibition) or adopted a latent variable approach to elucidate the specific contribution of cognitive flexibility toward the outcomes of interest. Therefore, in this new project, we seek to better characterise the relationship between the CF construct and academic outcomes, creativity, problem-solving and socioemotional skills in the context of Singaporean young adults.

### Research aim and strategy

Prior research has signified CF’s theoretical and practical importance as a vital factor in optimising success. To better characterise the CF construct and clarify CF’s cognitive and social underpinnings, we proposed the current project to investigate the relationships between CF, other executive functions, and other critical cognitive and social constructs in a Singaporean cohort. Specifically, the study aims to confirm whether there is a relative dissociation between CF and other executive functions (such as working memory and inhibition). We further aim to assess relationships between CF and other primary outcome variables, including structure learning, creativity, literacy, numeracy, and problem solving. Finally, the research aims to assess the influence of vital socio-cognitive variables (e.g., multilingualism, perceived social support, tolerance of uncertainty, and social decision-making) on these relationships. Understanding these relationships has value for translational research, such as in organisational settings (e.g., decision-making, career), and informs the need for CF training and development in the local educational curricula. The main hypotheses are summarized below.

Latent variable analyses will show relative dissociation between cognitive flexibility and other executive functions (such as working memory and inhibition).Cognitive flexibility will be relatively dissociated from general intelligence.Cognitive flexibility will be best represented by more than one latent variable.Structure learning scores will be associated with at least one of the cognitive flexibility latent variables.Cognitive flexibility latent variable(s) will be associated with at least one primary outcome variable (creativity, literacy, numeracy, and problem solving)The relationship between structure learning scores and cognitive flexibility will vary significantly at different levels of each primary socio-cognitive variable (multilingualism, perceived social support, tolerance of uncertainty, and decision-making factors).

The current study is part of a large-scale international collaboration under the University of Cambridge-Nanyang Technological University Centre for Lifelong Learning and Individualised Cognition (Cambridge-NTU CLIC). CLIC launched as a flagship research programme within the National Research Foundation of Singapore’s Science of Learning initiative and aims to improve support for lifelong learning and cognitive agility. The following protocol describes an adult characterisation study which aims to investigate the construct validity of CF and CF’s relationship with other cognitive constructs of interest. Thereafter, this study will be referred to as the “CLIC adult study”, as distinct from a related study (not reported here) that will be conducted with adolescents. Results of this study will inform the development of intervention paradigms to enhance CF (i.e., through structure learning-based training). CLIC projects also include adolescent studies and intervention studies, which will be reported separately.

## Methods

### Methods overview

The CLIC adult study protocol will be described in three main sections: Study Preparation, Study Administration Part I (Demographics, social questionnaires, and social decision-making tasks), and Part II (Cognitive tasks). Fig 1 summarises the overall study workflow. Study preparation encompasses recruitment, eligibility screening, and consent procedures. Study Administration Part I is delivered online, including demographics, socio-cognitive questionnaires, and social decision-making tasks. Part II of the study, the cognitive task battery, is administered in a lab or a hybrid remote-guided testing setting, based on participants’ preferences and suitability for online task administration.

**Fig 1 pone.0286208.g001:**
[figure not shown]
Overall workflow of the CLIC Phase 1 adult study. Detailed documentations of all tasks and questionnaires can be found in Appendices A to F in S1 File.

### Study preparation

#### Ethics

This study has obtained ethical approval (IRB-2021-761 "Executive Functions and Learning") from the Nanyang Technological University Institutional Review Board (IRB). Written consent from all participants will be obtained for this study.

#### Recruitment overview

Participants in this study will be Singaporeans recruited from vocational institutions (such as the Institute of Technical Education), institutions of Higher Education (NTU, other local universities and polytechnics), as well as from the general working population via community sampling (e.g., community centres, clinics, via social media platforms). Interested participants will be provided with a study sign-up webpage. The recruitment phase will commence on November 22, 2021, and will continue until January 22, 2024, or until the desired sample size has been reached, whichever occurs first. Access to information that could identify individual participants will only be granted to the Principal Investigator, Co-Principal Investigators, and key research staff assigned to manage personal data, such as for contacting the participant to schedule for an experiment.

#### Eligibility screening and consent

Upon signing up for the study, participants are requested via email to complete the eligibility screening questionnaire (Appendix A in S1 File) online. Participants’ responses to the screening questionnaire will be used to determine their eligibility for this study. See Appendix A in S1 File for the detailed inclusion criteria. Eligible participants will have the study information sheet and consent form sent to them via Adobe sign. They will have their queries or concerns answered through email or a virtual meeting with a research staff before consenting to the study. Afterwards, the participant will be assigned a participant ID for the study.

#### Sample size

We aim to recruit up to 400 healthy young adults aged 18 to 30 years old inclusive, to achieve a final sample size of at least N = 347. This sample size calculation is based on a meta-analysis by Yeniad et al. [24], with a data structure that is similar to the present study, suggesting a tight distribution of pairwise correlations ranging between 0.2 and 0.3 (with isolated extremes 0.09, 0.36). Based on this meta-analysis, we conservatively expect an effect size of approximately r = 0.15. Fisher’s Z transformations would hence require an N of 347 to achieve 80% power with an alpha set at 0.05. Allowing for a 15% data attrition rate, this yields a recruitment target of N = 400.

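### At the stated 15% attrition, 400 recruits leave 340 participants, not the promised minimum of 347: a minor arithmetic inconsistency in the sample-size statement

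*Protocol article*

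**What the plan says.** The Sample size section of the protocol article gives a complete chain of figures.

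- Planning effect: "we conservatively expect an effect size of approximately r = 0.15".
- Analysable sample: Fisher's Z transformation is said to "require an N of 347 to achieve 80% power with an alpha set at 0.05". Whether the test is one- or two-sided is not stated.
- Minimum: recruitment is meant "to achieve a final sample size of at least N = 347".
- Attrition and target: "Allowing for a 15% data attrition rate, this yields a recruitment target of N = 400". The formula for this step is not given.

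The 400 is also a ceiling. The Sample size section words it as a maximum, and so does the Methods paragraph of the Abstract: "This study will recruit up to 400 healthy Singaporean young adults". The Recruitment overview closes recruitment at a calendar date "or until the desired sample size has been reached, whichever occurs first". The article mentions neither replacement of lost participants nor recruitment beyond 400.

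**The concern.** An attrition rate is ordinarily the share of enrolled participants whose data are lost. On that reading, a ceiling of 400, a loss of 15% and a final sample of at least 347 cannot all be true, because 85% of 400 is below 347. A reader would take it that the plan absorbs a 15% loss and still keeps its minimum and its 80% power, and it does not quite do so. The allowance may well be used: Table 1 of the article puts the burden at about 5 hours online over 21–27 days, followed by 8.5–9 hours of cognitive testing over three sessions.

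**Working it through.** **Inputs, all from the Sample size section:** r = 0.15; power 80%; alpha 0.05; required final N 347; attrition 15%; recruitment target and ceiling 400.

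**1. Reproduce the plan's 347.** The Fisher z formula is N = ((z for alpha + z for power) / atanh(r))² + 3, with atanh(0.15) = 0.1511.

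- Two-sided: ((1.960 + 0.842) / 0.1511)² + 3 = 346.6, rounded up to 347. This matches.
- One-sided: the same formula gives 273.6, so 274. This does not match.

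The 347 is therefore correct, and the test behind it is two-sided.

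**2. Step from 347 to the recruitment target.**

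- If 15% of recruits are lost: 347 / (1 − 0.15) = 408.2, so 409.
- If 15% of the final sample is added: 347 × (1 + 0.15) = 399.05, so 400.

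The stated 400 equals the second result. It is 9 below the first (9 / 400 = 2.25%).

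**3. What 400 recruits deliver.**

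- At 15% attrition: 400 × 0.85 = 340, which is 7 below 347 (7 / 347 = 2.0%).
- Largest attrition that keeps 347: 1 − 347 / 400 = 53 / 400 = 13.25%.
- If each recruit independently has a 15% chance of being lost (an assumption made for this check), the binomial probability of keeping at least 347 of 400 is about 18%.

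**4. Power at r = 0.15, two-sided alpha 0.05.** Power = Φ(atanh(0.15) × √(n − 3) − 1.960).

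| Participants analysed | Power |
|---|---|
| 340 | 79.2% |
| 347 | 80.0% |
| 400 (no loss) | 85.3% |

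The seven missing participants cost about 0.8 percentage points.

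**5. The same loss as a detectable correlation.** At n = 340, 80% power is reached at atanh(r) = (1.960 + 0.842) / √337 = 0.1526, which is r of about 0.151. At r = 0.20, the lower end of the main range that the section cites, power with 340 is Φ(0.2027 × √337 − 1.960) = Φ(1.76), about 96%.

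**The case against.** Four points can be made for the plan.

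*The effect is negligible.* This stands. A fall from 80.0% to 79.2%, or a detectable correlation of 0.151 instead of 0.150, lies within the rounding of an effect that the section itself calls approximate. That effect was also deliberately set below the cited range of 0.2 to 0.3.

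*347 is still attainable.* This stands too. A reader might infer that a ceiling of 400 can never deliver 347 participants or 80% power. The figures do not support that: with attrition of 13.25% or less, both are reached. The shortfall arises at the attrition rate the plan names, not at every rate.

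*The arithmetic route is not stated.* Also correct. A reader might infer that the authors multiplied by 1.15 where they should have divided by 0.85. The match with 399.05 makes this likely, but 400 could also be a round operational target. The inconsistency does not depend on the route, since 85% of 400 is 340 however 400 was obtained.

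*The 15% may be a margin over the final sample.* On that reading 347 plus 15% is 399.05 and the figures agree. But the text calls it an attrition rate and names no other base. In the usual sense, the loss then covered is 13.25%. If a margin was meant, the sentence should say so.

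It does not help that a journal article condenses a fuller protocol. The calculation is printed here in full, so this is an error in stated text and not an omission.

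**Conclusion.** The point holds as a minor arithmetic inconsistency that is wrong as written. At the stated 15% attrition, the ceiling of 400 gives 340 participants and about 79.2% power for r = 0.15, not at least 347 and 80%. This rests on attrition meaning the share of recruits lost, and on a two-sided test, which is the only version that reproduces 347.

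It would be going too far to conclude that the study is materially underpowered for r = 0.15. The shortfall is 7 participants and under one percentage point of power, and the 347 itself is correct.

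**What to change.** Reword the Sample size section so that the ceiling, the attrition rate and the final sample agree. Either of these does it:

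- Up to 400 recruited; 340 expected after 15% attrition; about 79% power for r = 0.15 (two-sided alpha 0.05). The minimum of 347 is then dropped or replaced by 340.
- Up to 400 recruited, which allows for about 13% attrition while retaining 347 (400 × 0.87 = 348).

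Both keep the ceiling at 400, so the Abstract need not change. The cost is a sentence, with either a slightly lower stated power or a slightly smaller stated allowance. Raising the ceiling to 409 in the Abstract and the Sample size section would also reconcile the figures, at the price of up to 9 more participants, but so small a gap does not require it. Whichever is chosen, add that the test is two-sided and that attrition is counted as a share of those recruited.

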#### Pre-registration

The current study protocol elaborates on our submitted pre-registration to the Open Science Framework [26].

### Study administration

Table 1 summarises the planned CLIC adult study administration, which comprises of two parts: Part I will be conducted online and Part II will be conducted either entirely in a lab (Face-to-Face, F2F condition) or in a hybrid Remote-Guided Testing setting (Hybrid RGT). All participants will first complete online socio-cognitive questionnaires and social decision-making tasks in Part I (details in section on Social Factors, and in Appendix B in S1 File). The items within each questionnaire/task will be presented in a fixed order, except for one section from the Clip-Q Singapore Language History Questionnaire.

**Table 1 pone.0286208.t001:** Study administration Part I and Part II summary.

	Part I	Part II
**Number of lab visits**	0	1 (Hybrid RGT), 2–3 (F2F)
**Test sessions**	Demographics, social questionnaires, and social decision-making tasks	Cognitive task battery
**Constructs of interest tested**	Demographics, multilingualism, perceived social support, tolerance of uncertainty, and social decision-making	Cognitive flexibility, working memory, response inhibition, general intelligence, creativity, literacy, numeracy, problem-solving
**Total time**	5 hours, over 21–27 days depending on participant’s schedule	8.5–9 hours, completed over 3 sessions
**Venue**	Home-based administration (Online)	Laboratory and online

**F2F:** Face-to-Face testing; **RGT**: Remote Guided Testing. Estimated durations include study set up, briefing, and breaks.

Part II can be administered flexibly via one of two testing modalities: Face-to-Face in-lab testing (F2F) and hybrid Remote-Guided Testing (RGT). To tackle the challenges posed by the global COVID-19 pandemic in conducting human psychological research, Leong et al. proposed a new mode of testing–Remote-Guided Testing, as a promising alternative to the traditional in-person testing mode while maintaining the quality of cognitive data collected [27]. With the easing of social distancing measures, the CLIC Cognition Team has adapted the RGT protocol originally developed in 2020 to a hybrid-RGT version in 2022, incorporating both in-person and online testing.

At the beginning of Part II, participants will complete a technical questionnaire to ascertain their eligibility for RGT (See Fig 1. Full questionnaire can be found in Appendix C in S1 File). The screening criteria include operating system compatibility for our testing software, minimum screen size and resolution, and wired keyboard and mouse connections. If the participant meets the necessary technical criteria, arrangements will be made to schedule them for the hybrid-RGT sessions, otherwise, they will be scheduled for F2F sessions.

After confirming the participants’ three sessions in Part II of the study, they will complete the same set of cognitive tasks. The cognitive task battery will be delivered both manually and on computerised study platforms, such as Cambridge Neuropsychological Test Automated Battery (CANTAB) (www.cambridgecognition.com), Inquisit 6 (Millisecond, 2019), Gorilla Experiment Builder (www.gorilla.sc), and iABC (iabc.psychol.cam.ac.uk/welcome), as detailed in the next section and in Appendix D in S1 File. The task orders will be deliberately randomised to control for order effects, depending on the allocation of tasks within each session. Participants will be randomly assigned to one of the three testing orders, as summarised in Appendix E in S1 File. The F2F sessions will be administered in a lab setting using a ThinkPad E14 laptop, wired mouse and earphones. The entire cognitive task battery, tested over three sessions, will take approximately 8.5–9 hours to complete. Appendix F in S1 File summarises the estimated task durations for each cognitive task.

